### Sample size {14}

It is planned to recruit 144 patients for the study. This corresponds to a recruitment rate of approximately 10 patients per study site and year. The primary objective is to establish whether personalized stimulation (Experimental Condition) is superior to non-personalized stimulation (Control Condition 1) and sham stimulation (Control Condition 2) regarding differences in FMA-UE at the end of intervention. A mean FMA-UE at baseline of 33 ± 12 [31] is expected. From the guideline [24] a minimal clinically significant improvement of 12 points on FMA-UE is derived, which leads to an effect size of 1.0. However, an effect size of 0.67 instead of 1.0 will be conservatively assumed, as a large placebo effect in the sham condition might be observed, and also in the non-personalized stimulation condition. The analysis will be done as an analysis of covariance (baseline adjusted) with overall F-test for the factor “study arm”. If the F-test is significant, according to the closed testing procedure (Hochberg Tamhane, Multiple Comparison Procedures, New York, 1987) no adjustment for multiple testing will be necessary for pairwise comparisons in the three arm situation. Assuming normal distribution of the primary outcome measure and an R-squared of 0.2 for the covariate (baseline FMA-UE) 36 evaluable patients per arm will be needed and, thus, 108 evaluable patients in total for the F-test (type 1 error 0.05, power 80%). This is based on the worst case scenario of an effect size for non-personalized stimulation = 0.67/2 = 0.335. Thus, on the one hand, it is ensured that in the case of unexpectedly positive results of the non-personalized stimulation, there will be enough power to proceed to subsequent pairwise comparisons. On the other hand, if standardized differences between study arms of 0.67 hold, there will be a power of 88% to confirm these differences (type 1 error 0.05, two-sided). To adjust for degrees of freedom for center, baseline, and 20% dropouts, 144 patients will be included, i.e., 48 per study arm. The sample size calculation was performed by PASS 2020.

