## Statistical methods

### Methods and analyses {20a, 20b, 20c, 21b}

The primary population is the intent‐to‐treat population. This population is defined as all randomized patients with Baseline measurement of the primary endpoint (inclusion criterium). The primary analysis will be done as Baseline‐adjusted analysis of covariance, adjusted for study center with a type 1 error of 0.05 (two‐sided for pairwise comparisons) with primary endpoint FMA‐UE measured at the last therapy visit. The study arm will be coded as a three level factor and in the first step an F‐Test for the overall null hypothesis (all three means are equal) vs. the alternative (at least two measures are different) will be done. If this test is significant, all three pairwise comparisons will be performed without correction for multiple testing. If the F‐Test is not significant, p‐values for pairwise comparisons will be calculated but have to be interpreted descriptively. In the case of a significant result (for the F‐Test) in this step, following the principle of testing hierarchically ordered hypotheses, the same strategy will be applied for follow‐up after three months. For the parameters of interest (effects within study arms and their differences between study arms) two‐sided 95% confidence limits will be calculated. In case of relevant imbalances between study arms regarding known prognostic factors, sensitivity analyses will be done adjusted for these factors. Analogous methods will be applied for the analysis of secondary endpoints (proportional odds model for ordinally scaled variables, logistic regression for binary variables, if possible baseline adjusted). Even though p‐values will be reported, all results have to be interpreted descriptively. Descriptive analyses will include means, standard deviations, and ranges for continuous normally distributed data. Medians and interquartile ranges will be calculated for non‐normally distributed data. Nominal, especially binary variables will be described using absolute and relative frequencies. Additionally, we will present line listings for AEs/SAEs. Missing values of primary and secondary endpoints will be imputed multiply using the method of Rubin. Predictor variables will be age (years), gender, study center and Baseline, which will be available in the intent‐to‐treat population (inclusion criterion). We will use 500 imputation samples; the seed will be the calendarial date of the first programming of the analysis program. An interims analysis is not planned. Exploratory subgroup analyses will be done for gender. Before breaking the code of the randomization a statistical analysis plan will be produced. Deviations from this plan will be documented and justified.. In case of premature termination of study centers or severe imbalance of prognostic factors between study centers, a sensitivity analysis non‐stratified for study centers will be presented.

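### The imputation model leaves out study arm, so imputed scores carry no treatment difference; at the planned 20% missing, F-test power drops from about 82% to about 60%

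*Protocol article*

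**What the plan says.** All of the analysis text is in the protocol article, Methods and analyses {20a, 20b, 20c, 21b}.

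- Primary population: intention to treat. "This population is defined as all randomized patients with Baseline measurement of the primary endpoint". A patient with no end-of-treatment score therefore stays in the primary test through an imputed value.
- Analysis model: ANCOVA on FMA-UE at the last therapy visit, adjusted for baseline and center. "The study arm will be coded as a three level factor", and an overall F-test comes first. The pairwise comparisons and the 3-month FMA-UE test depend on that F-test being significant.
- Missing data: "Missing values of primary and secondary endpoints will be imputed multiply using the method of Rubin". The model is then named: "Predictor variables will be age (years), gender, study center and Baseline". "We will use 500 imputation samples", and a rule for the seed is given.

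Study arm is not in the predictor list, and no sentence says that imputation is stratified by arm.

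Under Sample size {14}, "an effect size of 0.67 instead of 1.0 will be conservatively assumed", with half of it (0.335) for non-personalized stimulation as the worst case and an R-squared of 0.2 for baseline. This gives 36 evaluable patients per arm for 80% F-test power. Then: "To adjust for degrees of freedom for center, baseline, and 20% dropouts, 144 patients will be included".

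**The concern.** An imputation model has to contain the terms that the analysis model estimates. Here the analysis estimates arm effects, and the imputation model sets them to zero. A sham patient without a score is credited with part of any benefit of active stimulation, and an experimental patient without a score loses part of theirs. Two things follow.

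- **Bias toward no effect.** If a share p is missing in each arm, the pooled contrast is roughly (1 − p) times the true one.
- **Variance that is too large.** The shrunken estimator varies less from trial to trial than Rubin's rules report, because the imputation and analysis models disagree. Intervals are too wide and tests too conservative.

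The sample size was raised to 144 so that 20% dropout would not cost the F-test its 80% power. The imputation rule gives that protection away. Because the F-test opens the rest of the testing sequence, the loss carries through to the pairwise and 3-month tests. The Discussion ties a follow-on confirmatory trial to this result, so a missed or understated effect matters.

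**Working it through.** **Inputs.** Sample size {14}: means 0 (sham), 0.335 (non-personalized) and 0.67 (experimental) in SD units; SD 12 points; R-squared 0.2; two-sided alpha 0.05; 48 randomized per arm; 20% dropout. Recruitment {15}: six sites; average dropout of 17.1% in earlier trials. Strategies to improve adherence {11c}: 4/157 (2.5%) stopped for intolerance in one comparable trial.

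**1. The plan's own figures reproduce.** The noncentrality is λ = n·Σ(μᵢ − μ̄)²/(1 − R²). With n = 36, Σ(μᵢ − μ̄)² = 2 × 0.335² = 0.224, so λ = 36 × 0.224/0.8 = 10.1. F-test power is 80.8% (79.5% at n = 35), so 36 per arm is right. Pairwise power at 0.67 comes to 88.0–88.3%, against the stated 88%. Since 108/0.8 = 135, a total of 144 covers 20% dropout with some room.

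**2. Expected contrast under the rule as written.** The pooled mean is (0 + 0.335 + 0.67)/3 = 0.335, so imputed patients in every arm center on 0.335.

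- Sham: 0.8 × 0 + 0.2 × 0.335 = 0.067.
- Experimental: 0.8 × 0.67 + 0.2 × 0.335 = 0.603.
- Contrast: 0.603 − 0.067 = 0.536 = 0.8 × 0.67.

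In points, the planned effect is 0.67 × 12 = 8.04, and 0.8 × 8.04 = 6.43.

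**3. Simulation.** 48 per arm and six centers, with values missing completely at random and equally across arms. Normal-model multiple imputation with posterior draws, then ANCOVA on arm, baseline and center. The F-test uses the pooled multivariate Wald statistic. Rows use 3,000–4,000 runs with 100 imputations, except the row marked with the planned 500 imputations (1,000 runs).

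| Missing | True means | Contrast, no arm | F-power, no arm | F-power, arm included | F-power, complete case |
|---|---|---|---|---|---|
| 20% | 0/0.335/0.67 | 0.530 | 59.8% | 82.3% | 83.1% |
| 20%, 500 imputations | 0/0.335/0.67 | 0.529 | 59.6% | 81.6% | 81.7% |
| 17.1% | 0/0.335/0.67 | 0.550 | 65.7% | 82.9% | 83.7% |
| 10% | 0/0.335/0.67 | 0.598 | 78.5% | 86.7% | 87.3% |
| 2.5% | 0/0.335/0.67 | 0.656 | 89.5% | 90.7% | 90.9% |
| 20% | 0/0/0.67 | 0.527 | 76.0% | 91.6% | 91.9% |
| 20% | 0/0/0 | −0.001 | 0.8% | 4.5% | 4.7% |

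A separate simulation in points, with means 0/4/8, gave 6.4 instead of 8.0 and 60% against 83–84% at 20% missing. At 5% missing it gave 7.6 points and 86% against 90%.

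**4. The variance.** At 20% missing without arm, the mean Rubin standard error is 0.208, while the estimate's actual SD is 0.165. With arm included the two agree (0.208 and 0.206). This accounts for the pairwise power. Taking a critical value of about 1.98:

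- Without arm: Φ((0.530 − 1.98 × 0.208)/0.165) = Φ(0.72) ≈ 76%; simulated 76.6%.
- With arm: Φ((0.672 − 1.98 × 0.208)/0.206) = Φ(1.26) ≈ 90%; simulated 89.1%.

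For the half-size contrast of experimental versus non-personalized stimulation (0.335), power is 19% without arm and 36–38% with it. Even the higher figure is low because the difference is half as large; only the drop to 19% is due to the imputation.

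**The case against.** The omission and its direction are hard to dispute, so the serious objections concern size.

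- **Less may be missing.** The primary FMA-UE is taken on the last treatment day, after five working days. The 20% resembles the overall loss-to-follow-up rates under Recruitment {15}, and section {11b} provides for last-day assessments in patients who withdraw. At 10% missing, power as written is about 79%, close to plan. This stands as a condition on the 60%. But 20% is the figure the protocol uses to size this analysis, and the 2.5% counts intolerance only, so it is a floor.
- **The arm means are a worst case.** If non-personalized stimulation equals sham, power is 76% rather than 60%. This also stands. The 0/0.335/0.67 pattern is nevertheless the one that the 80% was computed on, and 76% still compares with 92% when arm is included.
- **The error is conservative and the trial exploratory.** No false-positive risk is created: null rejection falls to 0.8–0.9%. That limits the kind of harm. It does not remove the bias in the estimate on which a confirmatory trial would be planned.
- **Dropouts may not show the full effect.** Patients who stop early could have a smaller true effect, and the bias would then be smaller than 8.0 versus 6.4. The documents do not settle this. Drawing all arms from one pooled regression is not offered as a deliberate assumption about dropouts, and the variance mismatch does not depend on this point.
- **The later analysis plan could add arm.** It could, but this is not a detail left open. Predictors, number of imputations and seed rule are fixed here. Arm cannot safely be taken as implied, because center and baseline, which are also in the analysis model, are named.

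The secondary endpoints were not simulated. They share the predictor list, so dilution in the same direction is expected, but its size for ordinal scales and inpatient days is unknown.

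**Conclusion.** The concern holds and should be corrected before analysis. Followed as written, the imputation dilutes the primary contrast by about the missing share and overstates its standard error, so it performs worse than a complete-case ANCOVA. At the planned 20% missing and the means used for sizing, the contrast falls from 0.67 to 0.53 SD. F-test power is about 60%, against about 82% with arm included. Repeated simulations put these at 58–60% and 79–84%.

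The figures assume values missing completely at random, equal missingness across arms, and no center, age or gender effects on the outcome. With less missing the power loss shrinks and becomes slight near 2.5%, but under these assumptions the estimate is pulled toward zero whenever primary values are missing and the arms truly differ.

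**What to change.** State the imputation predictors, for primary and secondary endpoints, as: *study arm (three-level factor), age, gender, study center and baseline*. Imputing separately within each arm would also serve. Carry the same wording into the statistical analysis plan, which the protocol says is produced before the randomization code is broken.

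Two optional additions: report the complete-case ANCOVA adjusted for baseline and center as a check, and include an arm-by-gender term in the imputation that feeds the exploratory gender subgroup analysis.

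The cost is one model term and one sentence. No patients, data or procedures are added. At 20% missing the change restores the contrast to 0.67 and F-test power to about 82%, with null rejection at 4.5%.

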
### Plans to give access to the full protocol, participant level-data and statistical code {31c}

The study protocol will be available on https://www.medizin.uni-tuebingen.de/de/das-klinikum/einrichtungen/kliniken/neurologie/studien. Participant-level data can be provided anonymously.

All investigators have access to the final data set. Data acquired will be stored for at least 10 years in accordance with current data protection law.

## Oversight and monitoring

### Composition of the coordinating centre and trial steering committee {5d}

Sponsor of the trial is the University Hospital of Tübingen with [name], Director of the Department of Neurology & Stroke, as Sponsor Deputy and Principle Investigator. Coordinating Investigator is [name], Deputy Director of the Department of Neurology & Stroke. Biometrician is [name], Director of the Institute for clinical epidemiology and applied biometry, who will also provide and supervise the data management. The Project Management is carried out by the Centre for Clinical Studies (ZKS) of the University Hospital of Tübingen that will also provide monitoring, SAE-management and -reporting. An independent external international scientific advisory board is associated that will provide scientific guidance, and will also take responsibility as the Data Safety and Monitoring Board (DSMB). Manufacturer of the investigational device (bossdevice) is sync2brain GmbH that will provide technical support. At the coordinating center the study takes place in the DIN-ISO-certified TMS study center of the University Hospital Tübingen with an on-site study team with high expertise in performing TMS in stroke patients, certified study assistants with expertise in study-associated clinical ratings of stroke patients and medical doctors with research focus in TMS and neurorehabilitation of stroke patients. The Brain Network and Plasticity research group at the Hertie Institute for Clinical Brain Research with world-leading expertise in TMS, led by [name], supports the trial in data analyses.

### Composition of the data monitoring committee {21a}

An independent external international scientific advisory board will be associated with the BOSS-STROKE trial that will provide scientific guidance, and will also take responsibility as the Data Safety and Monitoring Board (DSMB). Six researchers with international renowned expertise in stroke trials and/or rTMS treatment and an independent biometrician have agreed to participate in the board. The DSMB will be informed of all safety-related events by the PI. The DSMB will meet in regular intervals every 12 months and monitor the safety and adequate course of the clinical trial. It has also to decide whether reasons for premature termination of the clinical trial have occurred (see also above, criteria for discontinuing or modifying allocated interventions). Based on its review the DSMB will provide recommendations regarding trial modification, continuation or termination. The DSMB members will have access to the unblinded data if deemed necessary for their evaluations. The DSMB Charter is available for review upon request at the coordinating study center.

### Adverse event reporting and harms {22}

Adverse events will be collected, reported and assessed using standardized procedures in accordance with the regulatory requirements. The management and reporting of adverse events is supervised by the Pharmacovigilance Department at the Clinical Trials Center (ZKS Tübingen). For the purpose of this trial, the period of observation for collection of adverse events extends from the first use of the device until 7 days after the last application of the device. Any deterioration in the state of consciousness or neurological, especially motor, deficits will be recorded during the study. The assessment of the severity of the event is in accordance to the Common Terminology Criteria for Adverse Events (CTCAE) criteria (version 5.0). The relationship between the use of the medical device and the occurrence of each adverse event will be assessed for causality and categorized by the sponsor investigator and the second assessor.

#### Harms

Repetitive transcranial magnetic stimulation (rTMS) is considered a non‐invasive, painless and safe method to treat patients with neurological or psychiatric disorders as long as the safety guidelines of the International Federation of Clinical Neurophysiology [17] are followed. There is worldwide experience with hundreds of thousands of patients treated with rTMS, and a high class of evidence for therapeutic efficacy has been demonstrated for several indications [7]. A very rare adverse event is an epileptic seizure induced by rTMS. Strokes imply an increased risk of epileptic seizures, but there is no evidence that rTMS is associated with a higher risk of seizure initiation in stroke patients compared with subjects without brain damage [33]. In the proposed BOSS‐STROKE study, this risk is likely even further minimized compared to other studies, because patients are monitored by continuous EEG and, thus, early epileptic seizure detection is possible and rTMS treatment can be stopped immediately.

EEG and electromyography (EMG) passively record electrical biosignals and have no side effects; irritation to the skin may be provoked by application of the electrode cream (EEG) or adhesive electrodes (EMG).

MRI is a very commonly applied diagnostic method. Severe adverse effects of magnetic fields and radio frequency are not known, as long as the standardized MRI inclusion / exclusion criteria are obeyed. Possible side effects are muscle twitching or irritation of peripheral nerves while the patient is inside of the MRI-scanner. Other side effects are headaches and tinnitus as well as heating of metallic tattoos.

All experiments will be performed in a suitable location in a University Hospital with a qualified medical doctor available on site throughout the treatment sessions.

#### Expected adverse events (AE), frequency and relief or treatment (see Table 2***)***

**Table 2 Tab2:** Expected adverse events (AE), frequency and relief or treatment

AE	Likelihood of occurrence	Relief/ Treatment	Prevention
Seizure	Very low	rTMS halt, treatment according to neurological emergency standards	Monitoring by EEG during rTMS
Slight/moderate Headache	High	usually subside spontaneously, standard analgesics (NSAIDs)	Not applicable
Hearing impaired	Very low	rTMS halt, treatment according to otolaryngology emergency standards	patients and treatment providers will be protected by earplugs
Syncope	Low	rTMS halt, treatment according to neurological emergency standards	Monitoring by EEG during rTMS
Presyncope	Low	rTMS halted, treatment according to neurological emergency standards	Monitoring by EEG during rTMS
slight/moderate (Local) Pain	High	usually subside spontaneously, standard analgesics (NSAIDs)	Not applicable
Dizziness	Low	rTMS halt	Not applicable

Expected adverse events are:- slight headache- slight discomfort on the skin surface- mild transient discomfort at the site of stimulation during stimulation

#### Adverse events that do not have to be reported

More than half of patients experience apparent post-rTMS adverse events, but a substantial proportion of these reported events are rather not related to the investigational treatment but occur as a consequence of the experienced stroke. This may lead to lower specificity for genuine complications of novel treatments and falsely inflate the number of adverse events associated with the therapy. Therefore, events that can be excluded from expedited reporting will be specified (Table 3a-b):

**Table 3 Tab3:** Adverse events associated with stroke, that do not have to be reported

a) Acute stroke-related deficits	
New neurological deficits which may appear within several days after stroke	Abnormal gaze (partial gaze palsy, forced deviation)
	Visual field (partial hemianopia, complete hemianopia, bilateral hemianopia)
	Facial paresis (minor paresis, partial paresis, complete palsy)
	Limb ataxia
	Sensory deficits (pinpricks)
	Dysarthria (mild to moderate, unintelligible)
	Neglect (partial, complete)
	Speech/comprehension deficits (mild to moderate aphasia, severe aphasia, mute)
Neurological deficits which may display post-stroke	Deterioration in level of consciousness
	Deterioration of neurologic deficits, especially motor deficits
Complications due to stroke	Cerebral edema, cerebral incarceration
	Need for external ventricular drainage or decompression surgery
b) Other Adverse Events (AEs)	
AEs that are likely observed in stroke patients	• falls with subsequent fractures • subsequent stroke or transitory ischemic attack • heart infarction • pneumonia • urinary tract infection • sepsis • dehydration • delirium

Patients with stroke may present with a variety of neurologic symptoms including alterations in vision, changes in speech, focal numbness or weakness, disequilibrium or alteration in level of consciousness, dystextia, dystypia, dysgraphia, aphasia, apraxia, neglect, as well as elementary motor, ataxic, and sensory deficits. Some new deficits may occur within the early subacute period after stroke, or already present ones can deteriorate poststroke (Table 3a). Other complications are likely observed in stroke patients in the early subacute period but do not qualify as adverse events with a relation to the rTMS treatment and therefore will not be reported (Table 3b).

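### The Table 3 exemption has two scopes: expedited reporting only, or no reporting at all of Table 3b events such as recurrent stroke, heart infarction and sepsis

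*Protocol article*

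**What the plan says.** The section of the protocol article headed Adverse events that do not have to be reported gives three kinds of statement about one list:

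- The introduction argues that many events after rTMS come from the stroke and would inflate the count attributed to treatment. It then says: "Therefore, events that can be excluded from expedited reporting will be specified".
- The title of Table 3 is "Adverse events associated with stroke, that do not have to be reported", with no mention of expedited reporting. The section heading omits it as well.
- The closing sentence, which refers to Table 3b, says that these complications "do not qualify as adverse events with a relation to the rTMS treatment and therefore will not be reported".

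Table 3a holds acute stroke-related deficits and complications, including worsening of consciousness or motor deficits and cerebral edema. Table 3b holds other events, among them "subsequent stroke or transitory ischemic attack", heart infarction, sepsis and falls with fractures.

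Elsewhere:

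- Adverse event reporting and harms {22}: "Any deterioration in the state of consciousness or neurological, especially motor, deficits will be recorded during the study". The same section has the causal relation to the device assessed for each adverse event by the sponsor investigator and a second assessor. It sets the observation period from first use of the device to 7 days after the last use.
- Composition of the data monitoring committee {21a}: "The DSMB will be informed of all safety-related events by the PI". Members may see unblinded data if they judge it necessary.
- Methods and analyses {20a, 20b, 20c, 21b}: "Additionally, we will present line listings for AEs/SAEs".

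**The concern.** An exemption from expedited reporting affects how fast an event is sent on. An exemption from reporting affects whether it enters the safety data at all. The article states both for the same table, and for Table 3b it gives a reason that fits only the second: the events are declared unrelated to rTMS before any has occurred.

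In a randomized trial with a sham arm, that relation is for the data to show. Recurrent stroke, infarction and sepsis are expected in this population whatever the treatment, so a single case says little about cause. The comparison of arms says more, but only if events are collected by the same rule in every arm. Treatment must start within 14 days of stroke onset, when background complications are expected and the comparison with sham is most needed.

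What is at stake is the completeness of serious-event data. The DSMB may stop the trial for severe adverse events (Stopping rules and exclusion of study centers), and a positive result is meant to lead to a confirmatory trial (Discussion). Both depend on these events having been captured.

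**Working it through.** No arithmetic applies. The documents give no rate for any Table 3 event and no figure tied to the exemption, so the check is a comparison of the texts.

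**Step 1. Scope within the Table 3 section.**

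| Statement | Scope | Covers |
|---|---|---|
| Introductory sentence | Expedited reporting only | Tables 3a and 3b |
| Section heading | Reporting, without limit | Tables 3a and 3b |
| Table title | Reporting, without limit | Tables 3a and 3b |
| Closing sentence | Not reported, because presumed unrelated | Table 3b only |

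Three of the four statements omit the word expedited. The rationale in the introduction concerns how many events are counted against the therapy, not how quickly they are sent, so it does not settle the matter for the narrow reading.

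**Step 2. Table 3b against the rest of the article.**

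- *Causality.* The adverse event section requires an assessment for each event by two assessors. The closing sentence fixes the answer for a whole class beforehand. Both cannot hold.
- *DSMB.* Recurrent stroke, heart infarction and sepsis are safety-related on any ordinary reading. The DSMB cannot be told of all such events if this class is not reported.
- *Listings.* The analysis section promises listings of AEs and SAEs. Under the broad wording it is unclear whether Table 3b events appear in them.

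**Step 3. Table 3a against the rest of the article.** The closing sentence does not reach Table 3a. Its exemption rests on the heading and table title alone, and the adverse event section says that worsening of consciousness or of neurological deficits is recorded. An event can be recorded and still be exempt from expedited reporting, so the conflict here is softer and a consistent reading exists.

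**Step 4. Consequence under each reading.**

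- *Narrow reading (expedited only):* the events are collected, assessed and available to the DSMB. Only the closing sentence, heading and title need correcting.
- *Broad reading (not reported):* Table 3b events drop out of the sham-controlled safety comparison. The section on who is blinded says that staff giving the treatment cannot be blinded, and adverse events are assessed at the treatment visits (V2 to V6). An unclear omission rule could therefore be applied differently across arms.

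Events later than 7 days after the last device use fall outside adverse event collection under either reading.

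**The case against.** The strongest reply is that the sentence introducing Table 3 and stating its purpose says "events that can be excluded from expedited reporting will be specified", and that the heading and title are shorthand for it. On that view the closing sentence is loose drafting in a condensed article, and the full protocol and DSMB charter, which are not shown, may be clear. Adverse events are assessed at every treatment session, withdrawals for adverse events are recorded in the CRF, and blinded raters measure FMA-UE, mRS and the Barthel Index after treatment and at 3 months. Seizure, the rTMS risk that the article highlights, is not in Table 3.

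Much of this stands, and it rules out three stronger readings that a reader might infer:

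- *That an imbalance between arms is hidden from the DSMB.* No text says so. It follows only if the broad wording overrides the introduction, the causality rule and the DSMB section.
- *That neurological worsening will go uncollected.* The adverse event section says that it is recorded, and net motor worsening by arm would also show in the FMA-UE.
- *That the safety output is confined to listings.* The analysis section introduces them as an addition, and tables by arm may be in the statistical analysis plan.

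The reply does not remove the Table 3b conflict. The closing sentence is a stated rule with a stated reason, not a detail left out for brevity, and a site could reasonably follow it. The functional scales do not identify recurrent stroke, infarction or sepsis as events.

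**Conclusion.** The concern holds as an internal contradiction with a possible safety consequence. For Table 3b it is firm: the closing sentence contradicts the introduction to its own table, the causality assessment of each adverse event and the commitment to inform the DSMB of all safety-related events. For Table 3a it is a weaker ambiguity, resting on a heading and a title.

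If the broad wording is followed, an excess of serious Table 3b events on active rTMS over sham could be missed by the DSMB and in the final report. That is a risk created by the text, not an established outcome. Its size cannot be given, because it depends on event rates that the documents do not state and on which wording the sites apply. The conclusion also assumes that the full protocol does not already resolve the conflict. If it does, only the article needs aligning. Correction during recruitment matters because events not recorded prospectively may be hard to recover reliably later.

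**What to change.** Reconcile the Table 3 section with the adverse event and DSMB sections:

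1. Limit the heading, table title and closing sentence to exemption from expedited reporting.
2. Delete the advance statement that Table 3b events are not related to rTMS, and leave causality to the two assessors for each event.
3. State that all Table 3a and 3b events in the observation window are recorded in the eCRF, assessed for causality, included in the AE/SAE listings and made available to the DSMB by arm.
4. Tell all sites which rule applies, and if any site has followed the broad wording, have it enter the omitted events.

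The cost is a change of wording and some extra eCRF entry. No new visits or procedures are needed, and sites keep the relief from expedited reporting that the introduction describes.
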